## Abstract

**Background:**

Attention deficit hyperactivity disorder (ADHD) is the most common neurodevelopmental disorder in childhood and adolescence, with a prevalence of 5% and associated difficulties and worse prognosis if undetected. Multimodal treatment is the treatment of choice. However, sometimes treatment can be insufficient or have drawbacks.

**Objective:**

This study protocol aims to demonstrate the effectiveness of cognitive training through the serious video game The Secret Trail of Moon (MOON) in improving emotional regulation in people with ADHD.

**Methods:**

This is a prospective, unicenter, randomized, unblinded, pre- and postintervention study. The groups will be randomized (MOON vs control) via an electronic case report form. The MOON intervention will be performed 2 times per week for 10 weeks (30 minutes per session). The first 5 weeks (10 sessions) will be conducted face-to-face at the Puerta de Hierro University Hospital, and the remaining weeks will be conducted via the internet at the participants’ homes. The total sample consists of 152 patients aged between 7 and 18 years. All participants have a clinical diagnosis of ADHD under pharmacological treatment. Data collection will be used to obtain demographic and clinical data. The data will be recorded using REDCap. Measures will be made through clinical scales for parents and objective tests of cognitive functioning in patients. Additional information on academic performance will be collected. The study has a power greater than 80% to detect differences. Student *t* test, 2-factor analysis of variance (ANOVA), and Mann-Whitney analyses will be performed according to each variable’s characteristics.

**Results:**

The study was approved by the Research Ethics Committee of the Puerta de Hierro University Hospital on December 14, 2022. As of September 26, 2023, we have enrolled 62 participants, and 31 participants have completed the study. This clinical trial was funded by the Comunidad de Madrid (IND2020/BMD-17544). The approximate completion date is March 2024.

**Conclusions:**

Serious video games such as MOON can be motivational tools that complement multimodal treatment for ADHD.

**Trial Registration:**

ClinicalTrials.gov; NCT06006871; https://clinicaltrials.gov/study/NCT06006871

**International Registered Report Identifier (IRRID):**

DERR1-10.2196/53191

## Introduction

Attention deficit hyperactivity disorder (ADHD) is the most common neurodevelopmental disorder diagnosed in childhood and adolescence, affecting about 5% of people worldwide [1]. In addition to the classical clinical triad of ADHD (inattention, hyperactivity, and impulsivity) [2], the existence of comorbidity, executive dysfunction, or emotional dysregulation can complicate the prognosis [3]. A greater severity of ADHD symptoms is correlated with greater emotional dysregulation in both children [4] and adults [5]. Emotion regulation involves intrinsic and extrinsic processes responsible for managing the appraisal and control of emotional reactions, emotion intensity, temporality, and goal orientation [6]. Emotional dysregulation has a severe impact on social skills, academic performance, and adaptive skills, leading to a higher rate of usage of treatment services [4]. This impact on emotional regulation manifests diversely across broad age ranges in ADHD from children to adults [7-9]. Emotional regulation issues, even in patients aged 5 years and younger, predict inattention later on [10]. Guidelines recommend that emotional dysregulation be treated before the age of 7 years [11]. ADHD is considered a chronic disorder with a high economic cost [12,13], high accident rate, and increased risk of mortality [14].

Multimodal treatment is the most effective treatment for ADHD, and it encompasses pharmacological treatment, psychological treatment, and psychoeducation for parents and teachers. Pharmacological treatment is the treatment of choice in children and adolescents with severe ADHD [15] and the most common treatment in high-income countries [16]. Approximately 70% of patients observe a positive change in symptoms in the short term due to stimulants [17]. However, some drawbacks such as the side effects of pharmacological treatment (insomnia, appetite suppression, and growth retardation) make some parents reluctant [18]. Moreover, medication is more effective for the core symptoms of ADHD than for the bottom-up mechanisms associated with emotional regulation [19]. Cognitive behavioral therapy can help with social skills and problem-solving [20]. However, motivational difficulties in ADHD [3] and low adherence to treatment [18] have led to the development of additional interventions complementing multimodal treatments. Some studies show promising results with cognitive training [21], metacognitive interventions [22], music [23], and video games [24]. However, the overall results show small effect sizes and difficulties in maintaining long-term benefits and transferability to daily life (generalizability and transferability) [25]. More evidence is needed with greater control of risk biases.

Video games provide immersive and engaging entertainment experiences. They have been extended as tools in the field of health (eg, promoting physical exercise through exergames) to others for cognitive training, as discussed in the reviews by Peñuelas-Calvo et al [24] and Rodrigo-Yanguas et al [26]. In particular, a recent systematic review [27] showed the potential use of video games in improving emotional regulation. Using video games for ADHD treatment may be beneficial for several reasons, including their attractiveness, customization to suit the player’s tastes, and immediate reinforcement [28]. Children and adolescents with ADHD have difficulties associated with poor verbal working memory (poor internal language), which can make it difficult for them to perform tasks. In addition, they may be more dependent on external stimuli (ie, they may have low intrinsic motivation), causing them to become bored earlier [3]. Therapeutic interventions based on gamification and video games can be a good strategy to decrease treatment dropout rates by encouraging patients to perform tasks as games.

The Secret Trail of Moon (MOON) is a serious video game based on cognitive training for people with ADHD. It comprises a set of different mini-games focused on enhancing the most affected cognitive abilities in ADHD according to the Executive Functions and Behavioral Inhibition Model [3,29,30]. The games progressively increase in difficulty according to the patient’s needs. MOON was designed by a multidisciplinary team following a user-centered model (usability study) and an iterative redesign process [28,31]. Prior to this clinical trial, we completed another clinical trial. In that prospective, single-center, randomized clinical trial with 3 arms, MOON was tested in clinically stable patients with ADHD (on medication) aged 12 to 22 years (NCT04355065) for 3 months. The 105 patients were randomly assigned to the 3 groups: (1) cognitive training (12 sessions) with face-to-face MOON (n=31; 30); (2) cognitive training with online therapeutic chess (n=24; 23); and (3) control group with telephone monitoring (n=34; 32%). Contrary to our expectations, we did not find any statistically significant improvement in executive functioning, which was the primary outcome. However, we found some improvements in secondary outcomes, such as emotional intelligence, emotional regulation, and performance in the school context in both self-reports and parent reports [32]. Following these encouraging results, we designed the present clinical trial (NCT06006871) with the limitations of the previous clinical trial in mind, namely: (1) increasing sample size; (2) increasing the number of cognitive “doses” (20 sessions) and the access to the platform using virtual reality (VR) and computer interfaces; (3) improving some aspects of the MOON video game, particularly emotional regulation, such as the aesthetics of the virtual environment, the introduction of music [23], rhythm-based gameplay, and motivational elements such as the reward system; and (4) simplifying the design (2 arms, case versus control, instead of 3 arms). The main objective is to test the efficacy of MOON in improving emotional regulation in patients aged 7 to 18 years with a clinical diagnosis of ADHD.

## Methods

### Ethical Considerations

This study was approved by the Research Ethics Committee of the Puerta de Hierro University Hospital on December 14, 2022 (PI 106/22). Authorization from the Spanish Agency of Medicines and Health Products was granted on February 14, 2023 (1061/22/EC-R). Informed consent will be requested from legal guardians and minors protecting their personal data to the provisions of the Organic Law (3/2018) passed on December 5, 2018, regarding personal data protection and guarantee of digital rights.

The Spanish Agency of Medicines and Medical Devices (AEMPS) authorized the clinical research with medical devices lacking Conformité Européenne (CE) marking on February 14, 2023 (1061/22/EC-R). The version approved by both entities was version 4 in the protocol, data collection, and recruitment material. The investigator's brochure was approved in version 3. The ethics committee requested the elimination of the rhythm-based game because it has not been previously tested in patients with ADHD. Monitoring of the clinical trial was deemed necessary.

### Study Design

This is a prospective, unicentric, randomized, unblinded, pre- and postintervention study with a concealed randomization sequence. The groups will be randomized (MOON vs control) via an electronic case report form (CRF). The interventional study model is a parallel assignment. The allocation ratio will be equal in both groups.

### Procedure

All participants will be recruited from the child and adolescent psychiatry outpatient clinics of Hospital Universitario Puerta de Hierro Majadahonda. The number of visits varies in each group—the MOON group will have 12 face-to-face visits, while the control group will have only 2 presential visits. The total duration of the research will be 90 days in total (3 months for each participant: 12 weeks including both the pre- and postevaluation periods; Figure 1). Table 1 summarizes all the visits.

**Figure 1 figure1:**
[figure not shown]
Duration of the research. MOON: The Secret Trail of Moon; SDQ: Strengths and Difficulties Questionnaire.

**Table 1 table1:** Study flow.

Visit and day	Preinclusion (D1)	Inclusion (D0)	Training (D1-D90)	Final (D90)
Explanation protocol	✓			
CGI^a^ (clinical)	✓			
Randomization		✓		
Informed consent		✓		
Data collection note		✓		
CGI (parents)		✓		✓
SDQ^b^ (parents)		✓	✓	✓
CPRS-HI^c^ (parents)		✓		✓
SNAP-IV^d^ (parents)		✓		✓
SDSC^e^ (parents)		✓		✓
BRIEF-2^f^ (parents)		✓		✓
CPT-3^g^ (patients)		✓		✓
Corsi cubes (patients)		✓		✓
CTMT-2^h^ (patients)		✓		✓
GASA^i^ (patients)		✓		✓
Academic mark		✓		✓
UKU^j^ (patients)			✓	
Satisfaction questionnaire				✓

^a^CGI: Clinical Global Impression Scale.

^b^SDQ: Strengths and Difficulties Questionnaire.

^c^CPRS-HI: Conners Abbreviated Symptom Questionnaire.

^d^SNAP-IV: Swanson, Nolan, and Pelham Rating Scale.

^e^SDSC: Sleep Disturbance Scale for Children for Parents

^f^BRIEF-2: Behavior Rating Inventory Executive Function, Version 2.

^g^CPT-3: Conners Continuous Performance Test, Third Edition.

^h^CTMT-2: Comprehensive Trail-Making Test, Second Edition.

^i^GASA: Game Addiction Scale for Adolescents.

^j^UKU: Udvalg für Kliniske Undersolgester.

For the MOON group, the total number of sessions with the video game will be 20 (twice a week, adjusted according to the availability of the participants). Participants in the MOON group aged 12 years and over will perform the video game sessions in VR, while those under 12 years will perform the video game sessions on a computer. All participants in the MOON group will perform the cognitive training with MOON following the same order of the games reflected in Table 2. Each session will have a maximum duration of 30 minutes (approximately 20 minutes of MOON gameplay). The first 10 sessions will be held in person at the hospital. For participants over 12 years of age, the researchers will help to manually calibrate the eye distance of the VR headset to adjust the quality of vision. For those under 12 years of age, researchers will perform computer-based support to ensure proper use and understanding of the video game tasks. The researcher will explain the task, adapting the instructions to each participant’s age. Once the researcher is assured of the understanding of the task, the difficulty level will be raised in a personalized way for each participant. Progress is signaled to the player by leveling up, parameters (eg, hits, errors, time taken), and stars earned (0 star=poor performance, must repeat the level; 1 star=acceptable performance; 2 stars=good performance; 3 stars=excellent) (Figures 2 and 3).

**Table 2 table2:** Gameplay order by sessions.

Mode			Onsite at the hospital																			At participants' homes																		
Sessions			1		2		3		4		5		6		7		8		9	10	11			12		13		14		15		16		17		18		19		20
**Games**																																								
	Smasher			1		2								1				2					1						2				1				2			
	Kuburi			2				1				2						1		2							1				1				2					
	Teka-Teki	1						2				1				2					1		2														1		2	
	Enigma	2								1				2						1					2				1		2								1	
	Chess					1				2						1					2				1		2						2		1					

**Figure 2 figure2:**
[figure not shown]
The Secret Trail of Moon (MOON) progress.

**Figure 3 figure3:**
[figure not shown]
The star system in The Secret Trail of Moon (MOON).

Parents in session 10 will receive a flash drive with the video game and training on how to use it at home. The last 10 sessions will take place at the participants’ homes on their computers and will be monitored via the internet by the researchers. Data collected in the game (eg, completed levels, hits, errors, or reaction times) will be automatically sent to the PlayFab (Microsoft Corp) data server. The parents of MOON group participants will be asked in advance to provide their consent for the collection of these data.

For the control group, participants will be followed up with weekly calls to parents during this period. During this follow-up, psychoeducational support about ADHD will be provided to the parents.

### Hypothesis

Our main hypothesis is that patients with ADHD using MOON will improve their emotional regulation more than the control group. The efficacy will be evaluated by measuring the change produced from the baseline evaluation (day 0) and the final evaluation visit (day 90), aiming for a decrease of 3 to 4 points in the global score of the Strengths and Difficulties Questionnaire (SDQ) filled by the patient’s parents.

As secondary hypotheses, the difference with the control group in measures such as ADHD core symptomatology, cognitive abilities, and academic performance will be assessed. Our secondary hypotheses are listed in Textbox 1.

Secondary hypotheses of the study.H2: Patients with Attention deficit hyperactivity disorder (ADHD) using The Secret Trail of Moon (MOON) video game will improve in core ADHD symptoms compared with the control group.H3: Patients with ADHD using MOON will improve their cognitive functioning compared to the control group.H4: Patients with ADHD using MOON will improve in academic performance with respect to the control group.H5: A change in platform (face-to-face, internet) will not entail differences in emotional regulation.H6: There will be no clinically meaningful side effects associated with the video game.

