### Analyses

#### Sample Size Calculation

Based on similar investigations with hypotheses that are centered around the administration of the SDQ [52], our sample size calculation shows the need to perform the study on approximately 152 participants with a diagnosis of ADHD to cover most of the possibilities with a Cronbach α of 0.05 and a statistical power of 80%, taking into account a 15% dropout rate. We performed the sample size calculation to contrast a mean in the control group of 11 points on the SDQ global score versus a 2-point mean drop (symptomatologic improvement) in the experimental group with a pooled SD of 4. This estimate covers other less conservative situations, such as a difference of up to 4 points.

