#### Study Population

The intention-to-treat (ITT) analysis population is defined as participants who are randomized and receive at least 10 sessions, and the per-protocol population is defined as participants who will complete 100% of the training. All analyses will be performed on the premise of the ITT analysis.

A 2-way analysis of variance (ANOVA) will be performed, with time (pre and post) and group (experimental vs control) as factors and each measure as dependent variable. The difference between the study groups will be considered significant when P<.05.

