#### Primary End Point Analysis

The main objective is to test the efficacy of the cognitive training treatment (MOON) in improving emotional regulation in patients aged 7 to 18 years who have a clinical diagnosis of ADHD. The effectiveness is evaluated by measuring the change produced between the baseline evaluation (day 0) and the final evaluation visit (day 90) in the decrease of 3 to 4 points in the global SDQ score evaluated by the parents. A decrease of 3 to 4 points on the postassessment visit (D70) concerning the preassessment visit (D0) will be considered an improvement in emotional regulation based on other similar studies [52].

Subsequently, 3 parent SDQ measures will be assessed: initial assessment (D0), midterm assessment (D45), and final assessment (D90) to evaluate hypothesis 5 (switching from face-to-face to web-based methods does not lead to differences in emotional regulation).

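### The primary end point text judges efficacy by a 3-to-4-point SDQ fall from baseline with no control contrast, the analysis text by a between-group test at P<.05; the two can disagree and neither is named as deciding.

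*Protocol article*

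**What the plan says.** All references are to the protocol article.

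- **Hypothesis.** The main hypothesis is comparative: "patients with ADHD using MOON will improve their emotional regulation more than the control group". The next sentence says how efficacy will be evaluated: by change from day 0 to day 90, "aiming for a decrease of 3 to 4 points in the global score of the Strengths and Difficulties Questionnaire (SDQ"), as completed by the parents. Control does not appear in that sentence.
- **SDQ For Parents** (under Psychometric Assessments). A fall of 3 to 4 points from D0 to the post-assessment is defined as an improvement in emotional regulation.
- **Primary End Point Analysis.** Effectiveness is evaluated by the change between day 0 and day 90 "in the decrease of 3 to 4 points in the global SDQ score evaluated by the parents". The definition then follows: "A decrease of 3 to 4 points on the postassessment visit (D70) concerning the preassessment visit (D0) will be considered an improvement in emotional regulation". This primary end point text names no between-group contrast.
- **Study Population.** Each measure is analysed by a two-way ANOVA with time and group as factors. The decision rule is: "The difference between the study groups will be considered significant when P<.05". No minimum size of difference is set.
- **Sample Size Calculation.** The control arm is assumed to average 11 on the global score. The contrast used for sizing is worded: "versus a 2-point mean drop (symptomatologic improvement) in the experimental group with a pooled SD of 4". The section adds: "This estimate covers other less conservative situations, such as a difference of up to 4 points".

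The criterion is also dated inconsistently: D70 in the definition, day 90 in the Hypothesis section and elsewhere in Primary End Point Analysis.

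**The concern.** The article gives two ways of deciding whether the game worked and does not rank them. One is a fall from baseline of 3 to 4 points. The other is a between-group difference at P<.05.

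The fall has no stated unit. It could be a responder definition for each child, a target for the MOON mean, or a target for the difference between arms. These are different quantities with different sampling behaviour.

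The choice matters in this design. The trial is unblinded, the primary outcome is rated by parents, and the MOON group has 12 face-to-face visits against 2 for control. A fall within the MOON arm contains parental expectation, extra contact and regression to the mean as well as any effect of the game. Randomisation makes the arms comparable, so regression to the mean and other shared changes cancel only in a between-arm contrast. Expectation and contact that differ by arm remain even there, but a before-after criterion removes none of these. If the deciding rule is left open, a small or null difference could be reported as success because MOON fell by 3 points, or a significant difference could be reported as failing the protocol's own definition of improvement.

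**Working it through.** **Inputs from the article.** Difference for sizing 2 points; pooled SD 4; alpha 0.05; power 80%; dropout 15%; 76 per arm, 152 in total; improvement threshold 3 to 4 points; significance at P<.05. Alpha is taken as two-sided, because that reproduces 152.

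**Step 1: the article's own figure.** The standardised difference is 2/4 = 0.5. A two-sided two-sample t-test at 80% power needs 63.8, so 64 per arm. Allowing for dropout, 64/(1 − 0.15) = 75.3, so 76 per arm and 152 in total. The stated figure reproduces exactly. A one-sided test would need 50 per arm, 59 after dropout and 118 in total, which does not match.

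**Step 2: smallest significant difference.** The article does not say whether SD 4 refers to scores or to changes, so the SD of change is an assumption: SD_change = 4 × √(2(1 − r)), where r is the pre-post correlation. At r = 0.5 it equals 4. The standard error of the difference in change is SD_change × √(2/n), and the smallest significant difference is t(.975, 2n − 2) times that. With n = 64, t = 1.979:

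| r (assumed) | SD of change | Standard error | Smallest significant difference |
|---|---|---|---|
| 0.3 | 4.73 | 0.837 | 1.66 |
| 0.5 | 4.00 | 0.707 | 1.40 |
| 0.7 | 3.10 | 0.548 | 1.08 |

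Across this range the test can be passed by a difference well short of 3 points.

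**Step 3: fall met, test not met.** MOON falls 3.5 and control falls 2.5, a difference of 1.0. With n = 64 and r = 0.5, t = 1.0/0.707 = 1.41 and P=.16. For r = 0.3 to 0.7, P runs from .23 to .07. With all 76 per arm retained, P=.13 at r = 0.5; at r = 0.7 the standard error is 3.10 × √(2/76) = 0.503 and P falls to .048, so this particular example sits at the boundary there. If control falls 3.0 instead, the difference is 0.5, and with 64 per arm P=.48 at r = 0.5 (.55 at r = 0.3, .36 at r = 0.7). The disagreement does not depend on one choice of numbers.

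**Step 4: test met, fall not met.** MOON falls 2 and control does not change. With n = 64 and r = 0.5, t = 2/0.707 = 2.83 and P=.005. At r = 0.3 it is still significant: t = 2/0.837 = 2.39, P=.018. The MOON mean fall of 2 and the difference of 2 both lie below 3.

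**Step 5: if the threshold is read as a between-arm difference.** Suppose the true difference is the planned 2 points, with SD 4 and 64 per arm. The chance that the observed difference reaches 3 is 1 − Φ((3 − 2)/0.707) = 0.079. The chance that it is significant but below 3 is Φ(1.414) − Φ((1.399 − 2)/0.707) = 0.72. With 76 per arm these become 0.06 and 0.80.

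**Step 6: if the threshold is read per child.** With no true change at all, a child's score falls by 3 or more with probability Φ(−3/SD_change): 0.23 at r = 0.5 and 0.17 at r = 0.7. This uses a normal approximation. A count of responders in the MOON arm alone would therefore say little without the control arm's count.

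**The case against.** The best defence is that the article already specifies a comparative test. The hypothesis is worded against control, the ANOVA has group as a factor, and P<.05 is applied to the difference between groups. The Hypothesis section speaks of aiming for 3 to 4 points, which is the language of a target. On that reading the test decides, and 3 to 4 points is the change hoped for or thought meaningful. This is a sensible reading, and the fix adopts it. But the article does not say so: it presents the fall as the way efficacy is evaluated, including under the heading Primary End Point Analysis.

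A reader might infer that the trial is wrongly sized, or that 2 points is a third success rule in conflict with the others. The document does not support either. Two points is a planning value, the article presents it as conservative, and 152 reproduces. At 64 per arm and SD 4, power is about 99% for a 3-point difference and above 99.9% for 4 points.

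A reader might also infer that an effect of the planned size must miss the 3-to-4-point fall. It need not. A fall within MOON and a difference between arms are different quantities: MOON −3.5 with control −1.5 meets the fall and gives the planned 2-point difference. The miss occurs if control barely moves, or if the threshold is meant as a between-arm difference. The article says nothing about which applies.

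Nor is this a detail that can be left to an analysis plan. The article states how efficacy is judged, in two ways that do not agree.

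**Conclusion.** The concern holds in this form: two criteria for primary efficacy stand side by side, a 3-to-4-point fall without control or unit and a between-group test at P<.05, and nothing says which decides. They can disagree in both directions. At 64 per arm and a change SD of 4, a MOON fall of 3.5 against a control fall of 2.5 meets the fall at P=.16, and a MOON fall of 2 against no change in control gives P=.005 while missing it.

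The exact P values rest on the assumed change SD, which corresponds to a pre-post correlation of 0.5. For correlations of 0.7 to 0.3 the smallest significant difference is about 1.1 to 1.7 points, so the conclusion does not turn on that assumption. The sample size and the choice of a between-group test are not in question. What needs settling, before the data are analysed, is which criterion decides the main hypothesis.

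**What to change.** 1. In Hypothesis and Primary End Point Analysis, state that the main hypothesis is decided solely by the between-arm difference in SDQ change at the final visit. This is the group-by-time contrast, preferably estimated with adjustment for baseline SDQ. Test it at two-sided P<.05 and report it with its 95% CI.
2. In SDQ For Parents and Primary End Point Analysis, keep the 3-to-4-point fall only as a secondary responder definition for each child. Give it one cut-off, fixed before analysis (for example a fall of at least 3), and compare the responder proportions between arms. The before-after wording can stay for this purpose.
3. State that a fall within the MOON arm is not by itself evidence of efficacy.
4. Use one day for the final SDQ throughout, so that the contrast and the responder definition refer to the same assessment.

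The number of participants and the assessments do not change. The cost is a protocol amendment while enrolment is under way (62 participants were enrolled by 26 September 2023, under a version already approved by the ethics committee and the regulator) and a success claim with less room for interpretation.

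### H5 claims that the platform change makes no difference, but the only stated criterion is a difference test at P<.05 with no margin, and a non-significant result cannot support that claim

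*Protocol article*

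**What the plan says.** The Hypothesis section (Textbox 1) lists H5 among the secondary hypotheses: "A change in platform (face-to-face, internet) will not entail differences in emotional regulation". The Primary End Point Analysis section repeats it as "switching from face-to-face to web-based methods does not lead to differences in emotional regulation" and names the data: three parent SDQ readings, "initial assessment (D0), midterm assessment (D45), and final assessment (D90) to evaluate hypothesis 5". It gives no contrast, test, margin or interval rule for H5.

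The only decision criterion is in the Study Population section: "The difference between the study groups will be considered significant when P<.05". It belongs to a two-way ANOVA "with time (pre and post) and group (experimental vs control) as factors and each measure as dependent variable", a model that has no D45 level.

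The Sample Size Calculation section covers the primary comparison only: a control mean of 11 SDQ points "versus a 2-point mean drop (symptomatologic improvement) in the experimental group with a pooled SD of 4", with 80% power, "taking into account a 15% dropout rate", giving about 152 participants. Under Procedure, every MOON participant has sessions 1 to 10 at the hospital and sessions 11 to 20 at home on a computer. Those aged 12 and over play in VR, and younger participants use a computer.

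**The concern.** H5 asserts that something is absent. A difference test can contradict such a claim but cannot establish it, because P of .05 or more is also what an imprecise comparison produces. With no margin, the article does not say how large a platform difference would matter. With only a P<.05 criterion, H5 could gain support only by failing to reach significance. Under that reading, more dropout or noisier ratings would make H5 easier to uphold.

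The question has practical weight. The Discussion expects that engagement may fall off in the home sessions, so a weaker second phase is plausible. A report that home delivery matches on-site delivery could follow from low precision alone.

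**Working it through.** **1. The plan's own sample size.** Inputs: difference 2, SD 4, alpha 0.05 (taken as two-sided), power 80%, dropout 15%. By the normal formula, n per arm = 2 × (1.960 + 0.842)² × 4² / 2² = 62.8, so 63; 63 / 0.85 = 74.1, so 75 per arm and 150 in total. The t-based calculation gives 64 per arm; 64 / 0.85 = 75.3, so 76 per arm and 152 in total. The stated figure is reproduced. It covers the between-arm primary comparison and nothing else.

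**2. A contrast that matches H5.** Comparing the home phase with the on-site phase means comparing two changes:

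C = (D90 − D45) − (D45 − D0) = D90 − 2·D45 + D0.

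This takes D45 as the boundary between phases, as the plan's use of that reading implies. With equal SD σ and equal correlation ρ between visits, Var(C) = σ²(1 + 4 + 1) + 2ρσ²(−2 − 2 + 1) = 6σ²(1 − ρ).

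**3. Assumptions.** σ = 4 is the planning SD. The number analysed is 76 × 0.85 = 64.6, taken as 64 per arm. ρ is not in the article, so 0.3, 0.5 and 0.7 are shown. Nor does the article say whether the contrast is between arms or within MOON, so both are shown.

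- SD of C = 4 × √(6(1 − ρ)) = 8.20 / 6.93 / 5.37.
- SE within MOON = SD / √64 = 1.02 / 0.87 / 0.67.
- SE between arms = SD × √(2/64) = 1.45 / 1.22 / 0.95.

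**4. What sizes of C mean.** Lower SDQ is better. A 2-point gain on site followed by a plateau at home gives 0 − (−2) = 2. A 2-point gain fully lost at home gives (+2) − (−2) = 4. For the between-arm version these values assume that the control arm has the same change in both halves.

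**5. Chance of a non-significant result** (noncentral t, two-sided 0.05):

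| True contrast | Comparison | ρ = 0.3 | ρ = 0.5 | ρ = 0.7 |
|---|---|---|---|---|
| 2 points | between arms | 72% | 63% | 45% |
| 2 points | within MOON | 52% | 38% | 16.5% |
| 4 points | between arms | 22% | 10% | 1% |
| 4 points | within MOON | 3% | 0.5% | <0.1% |

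The 95% CI half-width (t quantile × SE) is about 2.9 / 2.4 / 1.9 points between arms and 2.0 / 1.7 / 1.3 within MOON.

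**6. Could equivalence be shown if the true contrast is zero?** Power of two one-sided 5% tests ≈ 2Φ(margin/SE − t₀.₉₅) − 1, floored at 0. The article gives no margin, so these are illustrations. ±2 is the planning difference; ±3 is the lower end of the SDQ drop that the article calls an improvement.

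| Margin | Comparison | ρ = 0.3 | ρ = 0.5 | ρ = 0.7 |
|---|---|---|---|---|
| ±2 | between arms | 0% | 0% | 35% |
| ±2 | within MOON | 22% | 48% | 81% |
| ±3 | between arms | 32% | 57% | 87% |
| ±3 | within MOON | 79% | 93% | 99% |

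**The case against.** The strongest reply is that no sentence says P of .05 or more will confirm H5. The P<.05 rule refers to the study groups in a pre/post model, whereas H5 concerns a change that only MOON participants undergo. The contrast and margin may stand in a full protocol or analysis plan that is not shown. This is right as far as it goes: a reader might infer a written rule that non-significance proves H5, and the article contains none. What remains is that the article itself fixes both the no-difference wording and a difference test as its only criterion, and the two do not fit each other.

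A second reply is that the miss rates depend on the contrast. For the simple D90 − D45 change with a true effect of 2 points, they are 34% / 20% / 5% between arms and 9% / 2% / 0.1% within MOON. That is correct, and it is why no single percentage can be given as a property of the trial. But that contrast does not compare the two phases. If the on-site phase helped and the home phase added nothing, D90 − D45 would be zero and H5 would appear supported.

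A third reply is that H5 is one of five secondary hypotheses and leaves the primary result and the sample size untouched. That stands, and it limits the weight of the point.

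**Conclusion.** The point holds as a mismatch between claim and criterion. H5 is worded as no difference, the one stated criterion is a test for a difference, and no margin or interval is given. It should be corrected, but it does not threaten the primary analysis.

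The size is conditional on 64 analysed per arm, SD 4, equal correlation of 0.3 to 0.7 between visits, and the phase contrast above. A true 2-point contrast is then missed in 45% to 72% of trials between arms and in about 16.5% to 52% within MOON.

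Two stronger readings are not supported:

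- A reader might infer that losing the whole planned benefit at home would usually go unnoticed. That is a 4-point contrast, missed in 1% to 22% of trials between arms and in 3% or fewer within MOON. The 2-point case is a gain followed by a plateau.
- A reader might infer that the design cannot support H5 at all. Low equivalence power throughout (0% to 35%) is specific to the between-arm contrast at ±2. Within MOON, or at ±3, power ranges from 22% to 99%, depending on the correlation.

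**What to change.** - Do not judge H5 by P of .05 or more. Reword it as exploratory, for instance: *to estimate the difference in SDQ change between the on-site and home phases*.
- Name the phase contrast, (D90 − D45) − (D45 − D0), say whether it is between arms or within MOON, and report it with its 95% CI.
- Allow a statement of no relevant difference only if the 90% CI lies inside a margin fixed and justified in advance.
- State that platform is confounded with time and order. Every MOON participant has hospital sessions first and home sessions second, and those aged 12 and over also move from VR to a computer. Even a precise contrast cannot be attributed to platform alone.

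The cost is wording only, with no new data. The downside is that H5 becomes an estimate rather than a claim that can be confirmed, and it may be reported as inconclusive.
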